**Figure 2. f2:**
[figure not shown]
Study flow diagram of referral, screening and allocation of patients to the EFT-T study. Client Change Interview Protocol; CORE-OM, Clinical Outcomes in Routine Evaluation-Outcome Measure; DSM, Diagnostic and Statistical Manual of Mental Disorders; MEDI, Multidimensional Emotional Disorder Inventory; GAD-7, Generalized Anxiety Disorder-7; LSAS, Liebowitz Social Anxiety Scale; OASIS, Overall Anxiety Severity and Impairment Scale; ODSIS, Overall Depression Severity and Impairment Scale; OFSIS, Overall Fear Severity and Impairment Scale; OLSIS, Overall Loneliness Severity and Impairment Scale; OSSIS, Overall Shame Severity and Impairment Scale; PCL-5, PTSD Checklist for DSM-5; PDSS, Panic Disorder Severity Scale; PHQ-9, Patient Health Questionnaire-9; ; SCID-5-RV, Structured Clinical Interview for DSM-5 Disorders (Research Version); SCID-5-PD, Structured Clinical Interview for DSM-5 Personality Disorders; SMA, Severity Measure for Agoraphobia; SMSP, Severity Measure for Specific Phobia; YBOCS, Yale-Brown Obsessive-Compulsive Scale.

### Measures

***Assessment of participants.*** Potential participants will be assessed for principal diagnosis of depression, anxiety and/or related disorders as well as any other co-morbid condition using the SCID-5-RV and the SCID-5-PD. The MEDI, an emerging tool used in transdiagnostic research will also be administered. Demographic data as well as data related to presenting issues will be collected.

**SCID-5-RV.** The SCID-5 (
First *et al.*, 2015) is a semi-structured diagnostic interview for assessing the major DSM-5 diagnoses (formerly conceptualised as Axis I disorders). Presently, there is no reliability or validity data available for the SCID-5. However, many reliability studies of previous SCID versions have been published, typically reporting fair to excellent levels of agreement (e.g.,
Lobbestael *et al.*, 2011). Regarding validity, the SCID is often used as the gold standard in determining the accuracy of clinical diagnoses (e.g.,
Basco *et al.*, 2000).

**SCID-5-PD.** The SCID-5-PD (
First *et al.*, 2016) is a semi-structured diagnostic interview for assessing the 10 DSM-5 personality disorders in clusters A, B, and C. Presently, there is no reliability or validity data available for the SCID-5. Based on previous studies,
First et al. (2016) observed that with both the SCID-5 and SCID-5-PD, reliability is likely to be higher in cases of joint interviewing, where raters are well trained, where presentations are more severe, and where diagnoses have higher base rates in the population.

**MEDI** The MEDI (
Rosellini, 2013;
Rosellini *et al.*, 2015) is an experimental self-report questionnaire, still in development, which aims to assess transdiagnostic vulnerabilities and phenotypes that would allow a profile (as opposed to categorical) approach to emotional disorder classification. Participants are asked to score 55 items using a response scale that ranges from 0 (not characteristic of me/does not apply to me) to 8 (extremely characteristics of me/applies to me very much) resulting in composite scores on eight subscales; neurotic temperament, positive temperament, depressed mood, autonomic arousal, somatic anxiety, social evaluation concerns, traumatic re-experiencing and dissociation, and avoidance. A pilot study has reported convergent and discriminant validity of the eight MEDI subscales compared to other well-validated self-report questionnaires (
Rosellini, 2013).

**Demographic data** These will be collected as part of the pre-trial assessment and will include data regarding age, gender, relationship status, living arrangements, number of dependents, level of education attained, occupation and work history, and disability.

**Data related to presenting issues** As part of the same assessment process, a clinical interview will gather data about the history of the client’s presenting and other psychological difficulties, including past and current interventions, medication, suicidality, substance use and any other potential risk factors.

***Primary outcome measures.*** Severity of depression and anxiety symptoms will be measured at pre-therapy, post therapy (16 weeks; but also post last session in cases where the last session falls outside the range of 16 ± 2 weeks) and at 6-month follow up, using the OASIS, ODSIS and CORE-OM as primary outcome measures. In addition, the OASIS and ODSIS will be administered at the beginning of every session, as they are similarly used in an established cognitive-behavioural transdiagnostic treatment (UP;
Barlow *et al.*, 2017b). With the exception of where a participant has explicitly stated a wish to withdraw from the study, participants who drop out of therapy will be contacted by the research team and invited to attend for 16 weeks and 6-month assessments.

**OASIS** The OASIS (
Norman *et al.*, 2006) is a 5-item, continuous, self-report measure of anxiety-related severity and impairment designed for use across anxiety disorders as well as in cases of subsyndromal anxiety. Items ask about anxiety and fear as experienced by the respondent over the past week, and are scored on a five-point Likert scale ranging between 0 (None; Little to none) and 4 (Extreme; All the time), which are then summed to provide one total score. The scale has demonstrated excellent 1-month test-retest reliability, convergent and divergent validity (
Norman *et al.*, 2006) and strong sensitivity to change (
Norman *et al.*, 2013).

**ODSIS** The ODSIS (
Bentley *et al.*, 2014) is a 5-item, continuous self-report measure designed for use across heterogeneous mood disorders and with subthreshold depressive symptoms. Items ask respondents about their experience of depression over the past week, are scored on a five-point Likert scale ranging between 0 (None; Little to none) and 4 (Extreme; All the time) with scores summed to provide one total score. Good reliability and validity for the ODSIS has been reported (
Bentley *et al.*, 2014).

**CORE-OM** The CORE-OM (
Evans *et al.*, 2000) is a 34-item questionnaire measuring psychological distress across four domains; subjective well-being, problems or symptoms, life functioning and risk. Respondents are asked to score items in relation to how they have been feeling over the past week on a five-point Likert scale ranging between 0 (not at all) and 4 (most or all of the time), yielding four domain scores as well as overall total and total (minus risk) scores. Good internal and test-retest reliability, and good convergent validity with other measures of psychological distress have been demonstrated (
Evans *et al.*, 2002).

***Secondary outcome measures.*** Each participant will also be asked to complete at pre-therapy, post therapy (16 weeks; but also post last session where the last session falls outside the range of 16 ± 2 weeks) and at 6-month follow up, one of the following disorder specific measures (PHQ, PDSS, SMA-A, LSAS, SMSP-A, GAD-7, YBOC, or PCL-5), as determined by the principal diagnosis assessed at pre-therapy. Additionally, three newly developed measures, the OSSIS, OLSIS, and OFSIS, will be administered during the pre-therapy assessment, with those measures on which a client scores 8 or higher, thereafter administered prior to each session, post-therapy and at follow-up.

**PHQ-9** The PHQ-9 (
Kroenke *et al.*, 2001) is a nine-item self-report instrument intended to assess the existence and severity of symptoms of depression. Internal reliability of the PHQ-9 has been reported as excellent, while construct validity, external validity and test-retest reliability have all been satisfactory. A clinical cut-off score of ≥10 has been suggested (
Kroenke *et al.*, 2001).

**PDSS** The PDSS (
Shear *et al.*, 1997) is a 7-item self-report scale comprised of five items assessing the core symptoms of DSM-IV defined panic disorder, with or without agoraphobia, and two additional items rating work and social impairment. Items are scored on a 5-point Likert scale. Excellent interrater reliability, moderate internal consistency, and favourable levels of validity and sensitivity to change have been reported. A cut-off score of 8 has been recommended as identifying the presence of current Panic Disorder (
Shear *et al.*, 1997;
Shear *et al,*, 2001).

**SMA-A** The SMA-A (
Craske *et al.*, 2013a) is a 10-item measure that assesses the severity of symptoms of agoraphobia in individuals age 18 and older over the past 7 days. Items are scored on a 5-point Likert scale with average scores of 1 – 4, respectively indicating mild, moderate, severe, and extreme severity of agoraphobia. The use of the average total score was found to be reliable, easy to use, and clinically useful in American Psychiatric Association (APA) DSM-5 field trials.

**LSAS** The LSAS (
Liebowitz, 1987) is a 24-item scale designed to assess the range of social interaction and performance situations that individuals with social anxiety may fear or avoid. Good reliability and convergent validity have been reported for the self-report measure (
Fresco *et al.*, 2001). A cut-of score of 30 has been recommended as identifying the presence of SAD (
Mennin *et al.*, 2002).

**The Severity Measure for Specific Phobia – Adult (SMSP-A)** The SMSP-A (
Craske *et al.*, 2013a) is a 10-item measure that assesses the severity of symptoms of specific phobia in individuals age 18 and older over the past 7 days. The measure was designed to be completed by an individual upon receiving a diagnosis of specific phobia (or clinically significant specific phobia symptoms) and thereafter, prior to follow-up visits with clinicians. Items are scored on a 5-point Likert scale with averaged scores of 1 – 4 respectively indicating mild, moderate, severe, and extreme severity of specific phobia related distress. The use of the average total score was found to be reliable, easy to use, and clinically useful in APA DSM-5 field trials.

**GAD-7** The GAD-7 (
Spitzer *et al.*, 2006) is a 7-item self-report questionnaire assessing GAD symptoms over the preceding two weeks. Using the threshold score of 10, the GAD-7 has been reported to have a sensitivity of 89% and a specificity of 82% for GAD; it has also been reported as having good reliability, as well as criterion, construct, factorial, and procedural validity (
Spitzer *et al.*, 2006).

**The Yale-Brown Obsessive Compulsive Scale (Y-BOCS)** The Y-BOCS (
Goodman *et al*., 1989a;
Goodman *et al*., 1989b) lists 58 separate obsessions and compulsions and asks subjects to indicate whether they have experienced any of these in the past or experience any of these currently. Subjects are asked to identify the two most currently experienced upsetting obsessions and the two most upsetting compulsions. They are then asked to rate on a 5-point Likert scale a further 11 items relating to their experience of these obsessions and compulsions over the past 7 days. The scale yields an overall score, as well as scores on separate Obsessions and Compulsions subscales. The Y-BOCS can be completed by a clinician as part of a clinical interview or can be completed as a self-report measure. As a self-report measure, the Y-BOCS has been reported as showing excellent internal consistency and test-retest reliability (
Steketee *et al.*, 1996).

**PCL-5** The PCL-5 (
Weathers *et al.*, 2013) is a 20-item self-report instrument designed to assess symptoms of posttraumatic stress disorder (PTSD). It is an updated version of the PTSD Checklist, revised to take into account changes to the diagnosis of PTSD in DSM-5, and replacing both the military and civilian versions of the earlier measure. Respondents indicate the degree to which they were bothered by posttraumatic symptoms in the previous month using a 5-point Likert-type scale ranging from 1 (not at all) to 5 (extremely). Strong internal consistency test-retest reliability, and convergent and discriminant validity has been reported for the PCL-5 (
Blevins *et al.*, 2015).

***Qualitative measure***

**CCIP** The CCIP (
Elliott, 1999) is a structured interview that asks client about their experience of change (including change for the worse) since the beginning of therapy. Clients are asked for their perspective on those changes. They are also asked about helpful and problematic aspects of therapy.

### Assessors

Assessments will be conducted by doctoral level psychologists and by psychology graduates (typically at master’s level) under the supervision of a doctoral level psychologist. The SCID-5-RV and SCID-5-PD assessments will be audio recorded and archived for subsequent evaluation of adherence to appropriate testing conditions. All assessments including post-therapy self-report assessments will be conducted by a clinician other than the therapist.

### Sample size

A sample size of 40 participants was determined (using G*Power –
Faul *et al.*, 2007) on the basis of the comparison between and within the two groups across time, and allowing for research attrition. Moderate effect size (f= 0.25) was used as a determinant of meaningful between groups difference with statistical power of 0.80 and alpha level of 0.05. It is expected that the study is likely to detect change over time within the active treatment (EFT-T) and in-between the active treatment and the wait-list. As the current project is a feasibility study, exploratory use of these initial data should help in planning a definite comparative non-inferiority trial, comparing EFT-T and a standard transdiagnostic CBT.

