## Abstract

**Background: **Depression, anxiety and related disorders, including obsessive-compulsive disorders and trauma/stressor related disorders, have high prevalence, chronic courses and cause significant impairment. These disorders are also highly co-morbid, and appear to share etiology and maintenance factors. Recent developments have seen the emergence of transdiagnostic approaches that systematically address the common/shared features of these disorders. A key advantage of transdiagnostic approaches is that they can reduce the pressure on mental health professionals to be proficient in a plethora of single-disorder focused treatments. Currently almost all transdiagnostic approaches come from cognitive-behavioural therapy (CBT). However, not all clients prefer or benefit from CBT. Emotion-focused therapy (EFT) represents an evidence-based alternative to CBT. This study aims to examine a transdiagnostic adaptation of EFT (EFT-T) as a treatment for depression, anxiety and related disorders.

**Method:** The current study is a randomised controlled trial that aims to establish the efficacy of EFT-T vs. wait-list control in the treatment of depression, anxiety and related disorders. Up to 40 clients presenting in a psychology/counselling service will be randomly assigned to two conditions: EFT-T (n=20) and wait-list control, with delayed intervention (n=20). Primary outcome measures will be the Overall Anxiety Severity and Impairment Symptoms, the Overall Depression Severity and Impairment Symptoms, and the Clinical Outcome in Routine Evaluation – Outcome Measure. Disorder specific self-report measures will also be used to assess the main symptomatology of respective primary diagnoses. Clients will be assessed prior to therapy, at week 16, at end of therapy, and at 6 months follow-up.

**Discussion:** This study aims to provide an initial test of EFT-T as a transdiagnostic treatment for depression, anxiety and related disorders. It will provide estimates of effects sizes that can inform power calculations for a comparative trial, comparing EFT-T to a standard transdiagnostic treatment, CBT.

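### The 80% power stated for a moderate between-groups difference (f = 0.25) is in fact power for a difference of about 0.9 to 1.0 SD between arms

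*Protocol article*

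**What the plan says.** The Sample size section of the protocol article states "A sample size of 40 participants was determined" with G*Power, "on the basis of the comparison between and within the two groups across time, and allowing for research attrition". The effect size, its label and the power come in one sentence: "Moderate effect size (f= 0.25) was used as a determinant of meaningful between groups difference with statistical power of 0.80", with an alpha level of 0.05. The section then draws a conclusion, in which the wait-list is the comparator: "It is expected that the study is likely to detect change over time within the active treatment (EFT-T) and in-between the active treatment". It also describes the trial as a feasibility study whose data will be used in an exploratory way.

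The G*Power test, the number of measurements, the correlation between them and the attrition rate are not given. The Abstract gives 20 participants per arm. Statistical methods plans repeated measures ANOVAs tested at the 0.05 level and says that wait-list participants receive the active treatment after week 16. Pre-therapy and week 16 are therefore the two assessments at which treated and untreated arms can be compared.

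**The concern.** For two equal groups, Cohen's f is half the standardised mean difference, so a reader told that f = 0.25 is a moderate between-groups difference will take it as 0.5 SD. In a group-by-time interaction the same f describes a difference twice as large. The interaction is the between-arm test that gives about 40 at plausible correlations, so the label and the calculation refer to different effects.

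At stake is how the result is read. Someone who believes that the trial has 80% power for a moderate benefit would treat a non-significant between-arm result as evidence against such a benefit. At the correlations one would normally assume, the trial would miss a true 0.5 SD benefit about as often as not, or more often.

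**Working it through.** **Inputs.** From Sample size: f = 0.25, power 0.80, alpha 0.05, total 40. From the Abstract: two arms of 20. From Statistical methods: repeated measures ANOVA, with two controlled times (m = 2). Assumptions not in the article: correlation ρ, varied from 0.3 to 0.7 with 0.5 as reference; 15% attrition, which takes 34 evaluable to 34/0.85 = 40.

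**1. Reproducing 40.** For the within-between interaction, noncentrality is λ = f²·N·m/(1 − ρ), with 1 and N − 2 degrees of freedom.
- ρ = 0.5, N = 34: λ = 0.0625 × 34 × 2/0.5 = 8.5, power 0.807.
- ρ = 0.4, N = 40: λ = 0.0625 × 40 × 2/0.6 = 8.33, power 0.803.
- For comparison, ρ = 0.3 needs 46 and ρ = 0.7 needs 22. Three times needs 28 at ρ = 0.5 and 34 at ρ = 0.4.

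The stated total is therefore reproducible.

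**2. The same f as a between-groups effect.**
- Between-groups factor, λ = f²·N·m/(1 + (m − 1)ρ): at m = 2 and ρ = 0.5, 98 are needed (84 at ρ = 0.3, 110 at ρ = 0.7). Power with 40 is 0.43.
- Week-16 two-sample t-test, d = 0.5: 128 are needed. Power is 0.34 with 20 per arm and 0.29 with 17 per arm.

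**3. What f = 0.25 means in the interaction.** Take equal baseline means, and week-16 means that differ by δ SD. The four cell means are 0, 0, 0 and δ. After removing the row and column means, each cell's interaction residual is ±δ/4, so f = δ/4 and f = 0.25 gives δ = 1.0 SD. This does not depend on ρ. With three times, in the patterns tried, f = 0.25 means 1.06 to 1.22 SD.

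Check: the two-by-two interaction test is the t-test on change scores. The SD of change is √(2(1 − ρ)) = 1.0 at ρ = 0.5. With δ = 1.0 and 17 per arm, the squared noncentrality is 17/2 = 8.5, the same λ as in step 1, with the same power of 0.807. Simulation (40,000 runs) gives 0.806.

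**4. Power for 0.5 SD.** Here f = 0.5/4 = 0.125. At N = 40 and ρ = 0.5, λ = 0.015625 × 40 × 2/0.5 = 2.5, and power is 0.34. The detectable difference at 80% power is 0.909 SD of change with 20 per arm and 0.991 with 17 per arm. Multiplying by √(2(1 − ρ)) puts it on the outcome's SD scale.

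| ρ | Power for 0.5 SD, 40 evaluable | Power for 0.5 SD, 34 evaluable | Detectable (SD), 40 | Detectable (SD), 34 |
|---|---|---|---|---|
| 0.3 | 0.26 | 0.22 | 1.08 | 1.17 |
| 0.5 | 0.34 | 0.29 | 0.91 | 0.99 |
| 0.7 | 0.51 | 0.45 | 0.70 | 0.77 |
| 0.85 | 0.80 | 0.73 | 0.50 | 0.54 |

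**The case against.** The strongest reply is that nothing has been miscalculated. The section says that the comparison runs between and within groups across time, which fits the interaction and the planned ANOVAs, and for that test the inputs do give about 40. This stands. A reader might infer that 40 is an arithmetic error, or that the trial needs 98 or 128 participants. The document supports neither. A difference near 1 SD against a wait-list may be plausible, and for a feasibility trial 40 is not necessarily unsuitable.

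Nor is the interaction the only route to such a number. The time test also gives 34 with two times at correlation 0.5, but it does not compare the arms. The between-groups factor falls to 44 or 34 with three or four measurements and a correlation near zero, which is implausible for repeated symptom scores.

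A reader might also infer that a non-significant result would wrongly stop the follow-on trial. No significance-based rule is stated. Objectives asks for recruitment, adherence and retention rates and for estimates to inform later power calculations, and its condition that results be promising is not tied to a test.

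Finally, a condensed article may leave software settings to the full protocol, so their absence alone is no fault. What remains is an affirmative statement in the article that attaches 80% power to the wrong size of effect.

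**Conclusion.** The point holds as a misdescription of the powered effect, with the sample size itself reproducible. The text claims 80% power for a moderate between-groups difference. The calculation that yields about 40 gives that power for a large one: 1.0 SD between arms when there are two times and no baseline difference.

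For 0.5 SD, power is about 0.34 with 40 evaluable and 0.29 with 34 at correlation 0.5, and between 0.22 and 0.51 over correlations 0.3 to 0.7. Only a correlation near 0.85 with nobody lost would bring it to 0.80, and the section itself says that attrition was allowed for.

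The 1.0 SD equivalence does not depend on the correlation. The power figures do, and both the correlation and the figure of 34 evaluable are assumptions. The expectation that the trial is likely to detect a between-arm difference is therefore justified only if the true difference is around 0.9 to 1.0 SD or more (at correlation 0.5).

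**What to change.** Keep 40 participants and revise the Sample size text:

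- State that f = 0.25 refers to the group-by-time interaction from pre-therapy to week 16. If G*Power was run with other settings, give those and recompute the figures below.
- Replace the description as a moderate between-groups difference with the detectable difference: about 0.9 to 1.0 SD at correlation 0.5, or about 0.7 to 1.2 SD over correlations 0.3 to 0.7 with 34 to 40 evaluable. Label the correlation and the attrition rate as assumptions.
- Say that power for a 0.5 SD difference is well below 80%.
- For the between-arm comparison, replace the expectation of likely detection with an estimate and 95% confidence interval. This suits the plan in Statistical methods to report the magnitude of between-group effects.
- Quote figures for baseline-adjusted ANCOVA only if that analysis is adopted; the article plans repeated measures ANOVA.

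The cost is a few sentences. No participant, assessment or analysis is added, but the stated power becomes less favourable.

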### Data management

On referral to the project all potential participants will be given a referral code. Each participant who proceeds to pre-trial assessment by the research team will be given a unique study code which identifies the client as assessed for the study. Participants who proceed from assessment to the trial will then be given a unique trial code, which will identify the client and the corresponding therapist. Paper copies of all measures will be identifiable only by the study and/or trial codes.

All data will be stored in locked filing cabinets in locked offices in the counselling centre and/or the School of Psychology, Trinity College Dublin. All identifying paper data (e.g., GP referral information, signed consent forms; and forms listing participant codes) will be stored in a separate locked filing cabinet to all other anonymised data, and will be accessible only to the Trial Manager and to members of the research team involved in pre-therapy and post-therapy assessments. All audio/video and electronic data will be stored on encrypted hard drives.

In order to mitigate against data entry errors, all data will be double entered into two parallel datasets by two separate members of the research team, and the two datasets will be routinely audited and compared. Multiple imputation will be used for missing data. All regulations set by the Research Ethics Committee at the School of Psychology, TCD, as well as data protection regulations will be observed.

